Association between the evolution of troponin/NT-proBNP and CV abnormalities.Cumulative incidence of MACEs at 3, 6, 12, and 24 months. MACEs were defined as the composite outcomes of nonfatal stroke, nonfatal myocardial infarction, hospital admission for heart failure (HF), cardiac revascularization, and CV death.Overall survival *.Association between the evolution of troponin/NT-proBNP and MACEs.The difference in the evolution of hs-TnT/NT-proBNP/transthoracic echocardiography and electrocardiography parameters between combination therapy and monotherapy.Association between patient characteristics and troponin.Association between patient characteristics and NT-proBNP.Agreement between hs-TnT and hs-TnI levels at baseline, 3, 6, 12, and 24 months *.The proportion of severe immune-related non-CV toxicities (grades 3–5).Association between the evolution of troponin/NT-proBNP and severe immune-related non-CV toxicities (grade 3–5).Association between the evolution of troponin/NT-proBNP and overall survival.Association between the evolution of troponin and diastolic function (based on the recommendations of Nagueh et al. [42]).Association between the evolution of troponin and calcium score.

* These endpoints will also be evaluated in a preliminary analysis once 50 patients have reached their 3-month cardiac follow-up visit. The sample size was not adjusted for interim analysis as the release of preliminary results is not data-driven and does not affect the error structure of the trial. Study-level conclusions will only be made once the final results of the trial have been analyzed.

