### 2.5. Sample Size

Our primary endpoint is the cumulative incidence of troponin elevation in the first three months of ICI treatment, compared to baseline levels. In order to obtain a sufficiently precise estimate of this incidence, the sample size was calculated based on the width of the 95% confidence interval.

As of January 2021, we added troponin to our standard-of-care blood analyses in ICI-treated patients. Approximately 10% of our patients had troponin elevation according to the definition in Section 2.4.1. Therefore, we assumed a 3-month cumulative incidence of 10% in our sample size calculation. To estimate this incidence with a precision of 7.5%, we need to include 249 patients. Precision is hereby defined as the width of the 95% confidence interval.

The dropout rate in the first three months is anticipated to be around 10%, mainly due to deaths. Therefore, death will be accounted for as a competing risk in the primary analysis. Simulations using Weibull distribution for time to death and time to troponin elevation showed that adding 10% in the calculated sample size still leads to a precision of less than 7.5% in the estimation of the cumulative incidence with death as a competing risk. Therefore, 276 patients will be included in the study.

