### 2.6. Data Analysis

All patient data will be collected via REDCap (a Research Electronic Data Capture), a secure HIPAA (Health Information Portability and Accountability Act)-compliant Web-based application, using a standardized data collection form. Data needed for analyses will be extracted from REDCap [43,44]. For categorical variables, frequencies and percentages will be reported. Where values are missing, percentages will be calculated for the available cases, and the denominator will be mentioned. Continuous variables will be summarized as mean with standard deviation and range.

For the primary endpoint, the cumulative incidence of troponin elevation will be calculated with death as a competing risk. Cumulative incidences and corresponding 95% confidence intervals will be reported at 3, 6, 12, and 24 months and a cumulative incidence plot will be used to visualize the results.

Similarly, for the secondary endpoints elevation of NT-proBNP, CV abnormalities, and MACE, cumulative incidences and 95% confidence intervals will be calculated, considering death as a competing event.

Evolution of troponin, NT-proBNP, transthoracic echocardiographic, and electrocardiographic parameters over time will be first studied in a linear mixed effects model with a random intercept per subject to account for the correlation of measurements coming from the same individual. This model will be extended with patient and treatment characteristics and their interaction with time, to evaluate their impact on the evolution of these parameters.

The association between the longitudinal evolution of troponin levels and time-to-event endpoints (CV abnormality, MACE) will be studied in a joint model combining a linear mixed model for troponin and a sub-distributional proportional hazards model for the time-to-event taking into account death as a competing event for CV abnormality and MACE. Latent random variables and common covariates are used to link the sub-models for the longitudinal measurements with the competing risk failure time data. In this way, the association between the evolution of the longitudinal measurements and time to event can be evaluated. Furthermore, by modelling the time to event, the analysis of the longitudinal measurements is adjusted for non-ignorable missing data due to informative dropout caused by deaths.

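### Death-related dropout is called non-ignorable but is adjusted for only in the troponin joint model; the 24-month NT-proBNP, echo and ECG trajectories rest on a mixed model that assumes it is ignorable

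*Protocol article*

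**What the plan says.** Section 2.6 names two models for the longitudinal data.

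- **Mixed model, all parameters.** "Evolution of troponin, NT-proBNP, transthoracic echocardiographic, and electrocardiographic parameters over time will be first studied in a linear mixed effects model", with one random intercept per patient. The only stated extension is covariates: "This model will be extended with patient and treatment characteristics and their interaction with time".
- **Joint model, troponin only.** "The association between the longitudinal evolution of troponin levels and time-to-event endpoints (CV abnormality, MACE) will be studied in a joint model". Its longitudinal part is a linear mixed model for troponin. Its event part is a sub-distribution hazards model for CV abnormality or MACE, with death as a competing event. Of this model the section says that "the analysis of the longitudinal measurements is adjusted for non-ignorable missing data due to informative dropout caused by deaths".

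Section 2.4.2 lists more than the joint model covers. It includes the 24-month evolution of hs-TnT and NT-proBNP, the evolution of echo and ECG parameters up to 24 months, and the association of both markers with CV abnormalities and with MACE. It also lists: "Association between the evolution of troponin/NT-proBNP and overall survival".

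Section 2.5 gives the only dropout figure: "The dropout rate in the first three months is anticipated to be around 10%, mainly due to deaths". Section 2.6 declares all secondary outcomes exploratory.

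**The concern.** A likelihood-based mixed model gives valid trajectories when dropout depends only on observed values and the covariance structure is right. The plan itself describes dropout by death as non-ignorable. It then relies on the ignorability assumption for NT-proBNP, echo and ECG, and says nothing about the difference.

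If patients whose NT-proBNP is rising or whose LV function is falling die sooner, their later values are absent and the fitted average course is too flat. The trial could then describe NT-proBNP, LVEF or GLS under ICI treatment as more stable than it was. Three listed analyses also have no place in the stated joint model: NT-proBNP with CV abnormalities, NT-proBNP with MACE, and either marker with overall survival. In the joint model as written, death is only a competing event.

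**Working it through.** **1. Which outcome has which model (Sections 2.4.2 and 2.6)**

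| Listed secondary outcome | Stated model | Adjusted for death? |
|---|---|---|
| Evolution of troponin | Mixed model; also inside the joint model | Yes, in the joint model |
| Evolution of NT-proBNP, echo, ECG | Mixed model, random intercept | No |
| Troponin with CV abnormality, MACE | Joint model | Yes |
| NT-proBNP with CV abnormality, MACE | None stated | – |
| Troponin or NT-proBNP with overall survival | None stated | – |

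Troponin is not shorthand for both markers here. Section 2.4.2 separates endpoints that name both markers from those that name troponin alone (diastolic function, calcium score). The mixed-model paragraph of Section 2.6 also names NT-proBNP separately.

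**2. How many values could be lost by 24 months**

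Inputs: 10% dropout by 3 months and N = 276, both from Section 2.5. The document gives no 24-month figure, so the shape of the hazard is an assumption. All dropout is treated as death, although the plan says mainly. With a Weibull hazard of shape k, retention is S(24) = 0.9^((24/3)^k).

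- k = 1 (constant hazard): 0.9^8 = 0.430, so 57% lost, about 157 of 276. At 12 months the loss is 1 − 0.9^4 = 34%.
- k = 0.5: 0.9^2.83 = 0.742, so 26% lost, about 71.
- k = 0.25: 0.9^1.68 = 0.838, so 16% lost, about 45.

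**3. What the planned mixed model returns**

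All marker–death associations and variances below are assumptions. Higher values mean worse.

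*Simulation A.* N = 276; visits at 0, 3, 6, 12 and 24 months; true 24-month change 0.02 × 24 = 0.48 log units. SDs: intercept 1.0, slope 0.03 per month, residual 0.4. Death depends on the true current marker value, with a constant baseline hazard calibrated to 10% deaths by 3 months.

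| Death hazard ratio per log unit | Random intercept (SE) | Shortfall in SE | Random intercept and slope (SE) | Shortfall in SE |
|---|---|---|---|---|
| 1 | 0.480 (0.066) | 0 | 0.481 (0.065) | 0 |
| 1.5 | 0.396 (0.070) | 0.084/0.070 = 1.2 | 0.426 (0.064) | 0.054/0.064 = 0.8 |
| 2 | 0.342 (0.082) | 0.138/0.082 = 1.7 | 0.379 (0.080) | 0.101/0.080 = 1.3 |

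Part of the shortfall comes from omitting a random slope and not from non-ignorable dropout: (0.084 − 0.054)/0.084 = 36% at hazard ratio 1.5, and (0.138 − 0.101)/0.138 = 27% at 2.

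With a declining hazard (k = 0.5, 26–28% lost), the random-intercept estimates are about 0.44 and 0.42, and about 0.45 and 0.44 with a random slope. These shortfalls are about one standard error or less. With assumed monthly sampling at 57% loss, the random-slope model gives about 0.46 and 0.45 (few replicates, so indicative only).

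*Simulation B.* Same N and visits, random-intercept fit, true change 0.50, intercept and slope SD 1, residual SD 0.5, about 57–61% lost.

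- Death independent of the marker: 0.50.
- Death driven by the last observed value, equal slopes: 0.50.
- Death driven by the last observed value, slopes differing between patients: 0.39.
- Death driven by the random intercept only: 0.45.
- Faster worsening raises mortality, log hazard ratio 0.3 or 0.7 per SD of slope: 0.29 or 0.06.
- Association reversed, log hazard ratio −0.7: 0.93.

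B ties death directly to each patient's slope, so it shows direction better than likely size.

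**The case against.** **Several stronger readings are tempting, and the document does not support them.**

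- *That the trajectories will look too favourable.* The document gives no association of NT-proBNP, echo or ECG with death. Its Discussion cites two retrospective cohorts on troponin. One, in melanoma, found no association with survival; the other, in patients on pembrolizumab, found that elevated baseline levels predicted mortality. The simulations show no bias without dependence and the opposite bias when the dependence is reversed.
- *That the plan requires a joint model for every trajectory and breaks its own rule.* Section 2.6 introduces the joint model to study association with events and mentions the dropout adjustment as a further benefit. What stands is that the plan accepts non-ignorability as a premise and then relies on its opposite elsewhere.
- *That troponin and NT-proBNP could not be compared.* Both are fitted in the same mixed model first, so a like-for-like comparison exists.
- *That deterioration before death goes uncounted outside troponin.* Cumulative incidences of NT-proBNP elevation and of CV abnormality treat death as a competing event. Table 1 includes LVEF and GLS decline, so worsening observed before death is counted there. This limits the risk of a misleading overall picture but does not correct the trajectories.

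**Other points that stand.** The loss of 57% is the upper end of the range. More frequent blood sampling could reduce the bias for NT-proBNP if it is measured at each cycle, but echo is scheduled only at the five fixed visits. The simulated truth is the course had nobody died. The course while alive is a legitimate alternative target, so which trajectory should lead is a choice on which statisticians differ.

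**What does not stand** is that this is only detail left to the full plan. The article names a model for these outcomes, and the assumption behind that model conflicts with what the next paragraph says about deaths.

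**Conclusion.** The inconsistency is real and stands on the text alone. Deaths are called non-ignorable, the adjustment is stated for troponin with CV abnormality and MACE only, and the 24-month NT-proBNP, echo and ECG trajectories assume the contrary. The NT-proBNP associations with CV abnormalities and MACE, and both overall-survival associations, are not covered by the stated joint model.

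The consequence is conditional: the trajectories may be biased, favourably if worsening patients die earlier. The size is unknown. It depends on an unstated marker–death association and on a 24-month loss of roughly 16% to 57%. Under the assumptions of simulation A the bias runs from none to 1.7 standard errors, of which about a quarter to a third comes from the random-intercept choice.

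The outcomes are secondary and exploratory. The primary endpoint already treats death as a competing risk, and the sample size is unaffected. This is a cheap improvement of modest priority.

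**What to change.** In Section 2.6:

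1. Apply the joint model, with death as an event, to NT-proBNP, LVEF and GLS as well as troponin. Link each marker's mixed model through shared random effects to a cause-specific hazard for death.
2. Use the same model for the listed associations of troponin and NT-proBNP with overall survival, and extend the CV abnormality and MACE joint model to NT-proBNP.
3. Report the joint-model trajectory beside the plain mixed model, as a sensitivity analysis of the 24-month evolution.
4. State whether the target is the trajectory while alive, and state the ignorability assumption wherever the plain mixed model is used alone, for example for ECG parameters.

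Cost: plan wording and a few extra model fits on data already being collected, with no new patients or visits. The downside is slower fitting and an added distributional assumption, which is why the plain mixed model stays in the report.

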Cardiac markers such as high-sensitivity troponin I/T (hs-TnI/hs-TnT), BNP, and NT-proBNP are crucial in the diagnosis of CV diseases. For example, troponin is a well-known cardiac biomarker that has become indispensable in the diagnosis of acute coronary syndromes. However, its role in cardio-oncology, more specifically in the active surveillance of ICI-mediated CV events, is not clear. Hence, the current guidelines are based on anecdotal evidence and expert opinions, due to the lack of solid data and prospective studies [33,37]. Therefore, cardiac monitoring, in patients receiving ICIs, is not always implemented by oncologists, as many questions remain unanswered:How should hs-TnI/hs-TnT levels be graded? The Common Terminology Criteria for Adverse Events (CTCAE, Version 5) is widely accepted as the standard classification and severity grading scale for adverse events in cancer therapy, clinical trials, and other oncology settings [38]. However, the current grading system makes it challenging to accurately document and report the severity and incidence of increased cardiac troponins, leading to ICI-induced CV toxicity. Furthermore, BNP and NT-proBNP are not even listed in the current CTCAE criteria.What are the cut-off values for cardiac markers for clinically meaningful changes in ICI-treated patients? When do further investigations need to be performed? (The upper limit of normal (ULN) is determined on a healthy patient population).What is the appropriate time interval between the testing of cardiac markers?What is the appropriate monitoring duration of cardiac markers? Three months or longer?

Our narrative review summarized previously conducted research regarding troponin levels in patients receiving ICI [39]. As prospective data are lacking, we initiated a multicenter, prospective trial (NCT05699915) in which patients with a solid tumor eligible for ICI treatment, i.e., anti-CTLA-4, anti-PD-1, and/or anti-PD-L1, will be enrolled. Patients receiving concurrent systemic antineoplastic treatment will be excluded in order to have a homogeneous treatment population. The patients included in this study will receive a thorough CV work-up at baseline and at regular time points during treatment for a total period of two years. Our aim is to study cardiac markers in patients receiving ICI therapy and to explore the association between CV abnormalities and major adverse cardiac events (MACEs).

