#### 2.4.1. Primary Endpoint

The incidence of an elevated hs-TnT above the ULN if the baseline value was normal; or 1.5 ≥ times baseline if the baseline value was above the ULN within the first three months of treatment. The maximum measured value will be taken into account *.

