Agreement between hs-TnT and hs-TnI (measured in all patients at baseline, 3, 6, 12, and 24 months) will be assessed in Bland–Altman curves and intraclass correlation coefficient (ICC) based on a two-way mixed effects model. The ICC and 95% confidence interval will be reported. Statistical analyses will be performed using R Software version 4.1.2 or higher.

As our clinical trial is an exploratory trial, secondary outcomes will be treated as exploratory results. Therefore, any definite finding for secondary outcomes will require further confirmatory studies to support possible findings. Hence, it is not needed to adjust for multiple testing for multiple secondary outcomes [45].

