## 3. Discussion

Since 2020, CV follow-up has become a “hot topic” in ICI-treated patients. Shortly after our study was initiated, other research groups started publishing their results on similar CV screening programs in patients receiving ICIs.

To determine the role of GLS, global circumferential strain (GCS), and global radial strain (GRS) in ICI-treated patients, Quinaglia et al. conducted a retrospective study in which 75 patients with ICI myocarditis were compared with 50 ICI-treated patients without myocarditis [46]. They found that GLS, GCS, and GRS can predict CV events with better accuracy than LVEF, hs-TnT, and age, in patients who were diagnosed with ICI-induced myocarditis. However, only limited paired data were available for the analysis. Furthermore, pre-ICI TTEs were not investigated and TTEs during treatment were performed at different time points.

Kurzhals et al. retrospectively analyzed pre-treatment hs-TnT levels in 47 patients who subsequently received ICI therapy for locally advanced and/or metastatic melanoma [47]. One patient, who had normal pre-treatment hs-TnT, developed myocarditis. 28% of the patients had elevated levels at baseline, however, none developed ICI-induced myocarditis. There was no association between hs-TnT and overall survival. However, patients were only monitored for a short period of time.

Waissengein et al. performed a retrospective analysis in 135 patients treated with first-line pembrolizumab to evaluate whether baseline and longitudinal changes in hs-TnI could serve as a predictor for the development of MACEs and survival [48]. They found that abnormally elevated baseline hs-TnI levels (>50 ng/L) and levels prior to the second dose served as significant independent predictors for MACEs, with over an eightfold increase in relative risk. In addition, elevated baseline levels had a predictive role in all-cause mortality. However, troponin levels were only evaluated prior to the start and at cycle two. Echocardiography was only performed in 53 patients at baseline and 27 patients in follow-up. Therefore, the role of hs-TnI in the development of LV dysfunction could not be assessed. Moreover, some patients (27%) also received pembrolizumab in combination with other types of chemotherapy, which can also influence the effect on MACE and survival.

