Nishikawa et al. conducted a prospective study on 100 patients eligible for ICI treatment [58]. An ECG was taken every month along with hs-TnI and NT-proBNP measurements. A 3D echocardiography (IE 33 imaging device, Philips Healthcare, Amsterdam, The Netherlands) was taken before treatment, at three months, and six months in order to determine the LVEF (modified Simpson method) and GLS. Myocardial damage was defined as an increase in hs-TnI levels by >26 pg/mL (Manufacturer’s cut-off value) and/or a decrease in LVEF by >10% to <53% on echocardiography. Ten patients (10%) developed myocardial damage within six months of treatment initiation. An increase in hs-TnI levels was noted in all ten patients, except one. However, this patient did have a decrease in LVEF from 57% to 41% along with an increase in NT-proBNP levels. GLS decreased by >15% in five of the patients. The authors noted that serial cardiac troponin I measurements could help detect early-phase myocardial damage by ICIs. It is important to note that 21 out of 100 patients received ICI therapy in combination with other systemic anti-cancer agents. Four of the ten patients that had myocardial damage received an ICI in combination with another systemic antineoplastic agent. Thus, the true cause of myocardial damage in these patients remains unknown. Furthermore, the patient’s risk factors for myocardial damage as well as prognosis were not further investigated in this study.

In conclusion, data regarding diagnosis, screening, and treatment recommendations on CV irAEs are insufficient. Guidelines that have been developed, however, are mostly based on expert opinions, retrospective studies, and case reports. Lately, more research has been conducted, however, should not only focus on the prediction and detection of ICI-induced myocarditis, as many other CV irAEs exist and should be taken into account. The results of this study will hopefully provide a better insight into cardiac biomarkers in ICI-treated patients and additional information in order to refine the current evidence-based screening recommendations and optimize risk stratification. Data from the CAVACI trial will be submitted to a peer-reviewed journal for publication.

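### Agreement of hs-TnT with hs-TnI is planned on levels by Bland–Altman and ICC; with different assay limits this could mislead about whether both markers flag the same patients

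*Protocol article*

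**What the plan says.** Section 2.4.2 lists as a secondary endpoint "Agreement between hs-TnT and hs-TnI levels at baseline, 3, 6, 12, and 24 months". It carries the asterisk, so it is also reported in the preliminary analysis once 50 patients have reached the 3-month cardiac visit. Section 2.6 fixes the method: agreement "will be assessed in Bland–Altman curves and intraclass correlation coefficient (ICC) based on a two-way mixed effects model", with the ICC and its 95% confidence interval. No scale, transformation or ICC form (consistency or absolute agreement) is stated, and nothing is planned on agreement of elevated versus not elevated.

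The trial's own rule for elevation, in Section 2.4.1, is relative and covers hs-TnT only: "The incidence of an elevated hs-TnT above the ULN if the baseline value was normal; or 1.5 ≥ times baseline" for patients who start above the ULN. The ULNs of the two assays used in the trial are not given. Section 2.6 adds that "secondary outcomes will be treated as exploratory results".

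**The concern.** Bland–Altman limits and an agreement ICC are built for two measurements of the same quantity in the same units. Troponin T and troponin I are different markers, each read against its own limit. The difference between the two in ng/L has no direct clinical reading, and if the markers are roughly proportional it grows with level.

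The Introduction motivates the trial by asking how hs-TnI and hs-TnT should be graded and which cut-offs matter clinically. The matching question about the two markers is whether they identify the same patients as elevated. A low ICC could be taken to mean that the markers disagree, and a high one that they are interchangeable. Neither follows from level agreement. The first report would rest on about 50 patients, where a few high values can dominate a raw-scale ICC if troponin is skewed.

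**Working it through.** **Figures in the plan.** The agreement analysis has no stated figure to reproduce. The sample size rests on the primary incidence alone ("we assumed a 3-month cumulative incidence of 10% in our sample size calculation") and reproduces: a Wilson 95% interval at 10% first has width 0.075 or less at n = 249, and 249/0.90 = 276.7 against the stated 276. Nothing below changes it.

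**Inputs, all assumed because the article does not give them.** hs-TnT is log-normal with log SD 0.6 or 0.9, and 10% of patients lie above its ULN. hs-TnI = k × hs-TnT, and the hs-TnI ULN is k times the hs-TnT ULN. The two markers then classify every patient identically by construction, and k is the ratio of the ULNs.

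**Formulas for raw levels.**
- Consistency ICC = 2k/(1 + k²)
- Absolute-agreement ICC = 2k/(1 + k² + (k − 1)²/CV²), with CV² = exp(SD²) − 1, which is 0.433 for SD 0.6 and 1.248 for SD 0.9

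Replacing k by 1/k changes neither, so it does not matter which assay has the higher limit.

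Example, k = 2: consistency 4/5 = 0.80; absolute 4/(5 + 1/0.433) = 0.55 and 4/(5 + 1/1.248) = 0.69.

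**Results (simulation of 200,000 patients; classification agreement 100% in every row).**

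| k | Consistency | Absolute, SD 0.6 | Absolute, SD 0.9 |
|---|---|---|---|
| 1 | 1.00 | 1.00 | 1.00 |
| 1.5 | 0.92 | 0.78 | 0.87 |
| 2 | 0.80 | 0.55 | 0.69 |
| 3 | 0.60 | 0.31 | 0.46 |
| 5 | 0.38 | 0.16 | 0.26 |

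The formulas agree to within 0.01. At k = 3 and SD 0.9 the Bland–Altman bias is 0.94 times the hs-TnT ULN, with limits of −1.13 to 3.02.

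**Rescaling.** Expressed as multiples of each assay's own ULN, both ICC forms return to 1.00. On log values only the consistency form does; the absolute form stays at 0.60–0.77 for k = 2. So the ICC form must be named as well as the scale.

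**Non-proportional relation.** Let hs-TnI in ULN multiples be hs-TnT in ULN multiples raised to the power 0.5 or 1.5 (SD 0.9). Classification is still identical, yet the ICC on ULN multiples is 0.76–0.80. Even a rescaled ICC is therefore not a measure of concordant classification.

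**The converse.** Take nearly equal levels (log-scale noise SD 0.1, hs-TnT log SD 0.9): ICC 0.99. If the hs-TnI ULN is twice the hs-TnT ULN, 10% exceed the first limit and about 2.1% the second. Treating the second group as contained in the first, observed agreement is 1 − (0.100 − 0.021) = 0.921, chance agreement is 0.10 × 0.021 + 0.90 × 0.979 = 0.883, and kappa = 0.038/0.117 ≈ 0.32. With a 3-fold ratio the simulated kappa is 0.11.

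**The case against.** The case on the other side has four parts.

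- **The article does not say that raw values will be used.** Transformation and ICC form are details that a condensed article may leave to an analysis plan, and a log-scale consistency ICC would be 1.00 under the proportional model. This stands, and silence on those details is not itself the fault. What remains is that the endpoint is worded on levels, the chosen methods assume a common scale, and no scale of these statistics shows whether the same patients are flagged.
- **The endpoint is agreement of levels, so the method matches it, and classification concordance is a different question.** That is partly fair. But the trial uses troponin clinically only through the ULN and the change from baseline, so level agreement alone says little about that use.
- **A Bland–Altman plot would show a difference that grows with level.** True, but the ICC and its interval would still be reported as the summary.
- **The endpoint is exploratory.** This limits the severity.

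A reader might go further and infer that poor agreement will be reported. The Discussion cites hs-TnI thresholds from other studies: "an increase in hs-TnI levels by >26 pg/mL" in one and a level above 50 ng/L in another. With an assumed hs-TnT ULN of 14 ng/L (not in the article) and log SD 0.5–1.0, the ratios 26/14 = 1.86 and 50/14 = 3.57 give consistency ICCs of 0.83 and 0.52, and absolute ICCs of 0.53–0.76 and 0.19–0.41. The article does not support this as a forecast. One threshold is an increase within a damage definition, the other a level that predicted events, and neither is stated to be this trial's ULN. Nor is agreement tested: no hypothesis or threshold for acceptable agreement is set.

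**Conclusion.** The concern holds as a possibility, not a certainty. As worded, the analysis can mislead in both directions about whether hs-TnT and hs-TnI flag the same patients. With identical classification, a raw-level ICC could be 0.55–0.80 if the ULNs differ 2-fold and 0.31–0.60 if they differ 3-fold. It stays at 0.78–1.00 for ratios of 1–1.5. With nearly equal levels and ULNs differing 2- or 3-fold, an ICC of 0.99 could accompany a kappa of 0.32 or 0.11.

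These figures rest on assumed log-normal values, a proportional relation (near-equality for the converse), analysis of raw levels, and 10% above the hs-TnT ULN. The actual ratio of ULNs cannot be read from the article. Severity is minor to moderate.

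**What to change.** 1. Make concordance of elevated status the lead agreement analysis at each paired visit: above own-assay ULN at baseline, 3, 6, 12 and 24 months, and from 3 months also the Section 2.4.1 rule applied to each marker against its own baseline. Give positive and negative percent agreement and kappa, each with a 95% confidence interval. Use the paired visit values for both markers, so that a maximum over many hs-TnT samples is not set against a single hs-TnI sample.
2. Keep Bland–Altman and the ICC as supporting analyses, on multiples of each assay's ULN or on log values rather than raw levels. Name the ICC form; on log values only the consistency form removes a constant scale factor.
3. State the two ULNs.
4. Apply the same wording to the preliminary analysis.

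The cost is wording only, because both markers are already measured in all patients at these visits. The downside is imprecision: if about 10% are elevated, the preliminary analysis would have about 0.10 × 50 = 5 such patients and 249 patients would give about 25. Kappa and positive agreement will have wide intervals, especially early, which is tolerable for an exploratory endpoint if the intervals are shown.
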